| Technical Summary (Max. 300 words) UK South Asian and African Caribbean people with type 2 diabetes experience worse diabetic control and more cardiovascular complications than the European-origin population; ethnic minority populations without diabetes also experience an excess of most types of cardiovascular disease. Explanations are unclear. Blood pressure and lipid control, crucial to cardiovascular risk reduction for people with and without diabetes, also differ by ethnicity. However, ethnic differences in prescribing for diabetes, hypertension and hyperlipidaemia remain understudied.  Ethnic differences in prescribing anti-diabetic (in people with diabetes), antihypertensive and lipid-lowering medication (in people with and without type 2 diabetes) will be sought, including: i) time to commencement ii) choice of medication, iii) dosage, iv) monitoring and iv) time to intensification (either medication up-titration, addition or class switching) after detection of sub-optimal control.  Primary care electronic medical records will be used. Established algorithms and code lists will define ethnicity, diagnoses and medication use. Data will be analysed using Kaplan-Meier time-to-event methods and logistic, Poisson and Cox regression models (according to outcome), with South Asian or African Caribbean ethnicity as the exposure (baseline category=European). These methods will allow for differences in follow-up time. The potentially confounding or mediating influences of age, sex, smoking, BMI, deprivation, polypharmacy, multi-morbidity, drug adherence, patient engagement and diabetes duration/ HbA1c will be explored. |
| D. Outcomes to be Measured Proportion of people eligible for antihypertensive or lipid-lowering medication who are prescribed the respective medication; Time to first anti-diabetic/ antihypertensive/ lipid-lowering medication prescription; Choice of anti-diabetic/ antihypertensive/ lipid-lowering medication; Dose of anti-diabetic/ antihypertensive/ lipid-lowering medication; Monitoring of anti-diabetic/ antihypertensive/ lipid-lowering medication; Time to anti-diabetic/ antihypertensive/ lipid-lowering treatment intensification. |

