| Study Background The UK’s largest ethnic minority groups, people of South Asian and African Caribbean descent, are disproportionately affected by type 2 diabetes (1), and most types of cardiovascular disease (2). UKPDS (UK Prospective Study of Diabetes) established the importance of tight blood glucose control in reducing CVD complications (3), but research suggests that glucose control is poorer in UK South Asians and African Caribbeans than Europeans (4, 5), despite their greater prevalence of complications (2). Yet the use of anti-diabetic medication in these groups remains understudied. Blood pressure and lipid control is key in reducing CVD risk in people with and without diabetes (6), therefore we will also examine prescribing patterns for antihypertensives and lipid-lowering medication.  UK guidelines recommend metformin as first-line anti-diabetic therapy, with several choices of further agents before insulin use (7). A recent study has reported on the choice of second-line treatments in CPRD (8; ISAC protocol number 16_267), with some indication that people from ethnic minority groups are less likely to receive newer anti-diabetic drugs. However, the influence of key factors such as diabetes duration and adherence to treatment were not accounted for, and the related questions of monitoring frequency and expediency of appropriate treatment intensification were not studied. Moreover, evidence from smaller primary care databases suggests South Asians and African Caribbeans are less likely than Europeans to receive insulin, and more likely to be on a higher number of oral diabetes drugs (5, 9). UK hypertension guidelines advocate calcium-channel blockers (CCBs) as first-line treatment for African Caribbeans, and ethnic differences in monotherapy are established (10), but little examination of ethnic differences in prescribing exists beyond this. Studies from aggregated primary care data indicate that statins may be under-prescribed in areas with large ethnic minority populations (11, 12), but were limited by analysis at area level.  Delay in anti-diabetic treatment intensification is linked to poorer subsequent control (13), but in spite of the poorer diabetic control in ethnic minority groups, ethnic differences in time to intensification have never been studied. Equally, an absence of research on ethnic differences in intensification of antihypertensives exists (14). However, previous research indicates that African Caribbean people are less likely than their white counterparts to be prescribed statins (15), though it is unclear if this is the case for people with diabetes. Additionally, whilst evidence from CPRD indicates that hypercholesterolaemia with high cardiovascular risk is inadequately treated in people with diabetes (16), scrutiny by ethnicity is lacking. |

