| Feasibility counts The primary analysis will be using data from CPRD alone (see section M for sensitivity analyses). Ethnicity recording for active patients is approximately 50% (17, 18). The ethnic breakdown is similar to that of the UK census 2011(20).  From 2000-2017, ≈280K patients initiated first-line and ≈80K second-line treatment for type 2 diabetes in CPRD (8). If 50% of these people had ethnicity codes present in their record, this would correspond to ≈140K starting first-line and ≈40K starting second line treatment. Using the 2011 census to calculate proportions, this would equate to ≈120.4K Europeans, ≈10.5K South Asians and ≈4.6K African Caribbeans initiating first-line treatment and 34.4K, 3.0K and 1.3K respectively starting second-line treatment. These are conservative estimates given the over-representation of ethnic minorities in the diabetic population.  Approximately 77% of the people with diabetes initiating first-line treatments are likely to be on antihypertensives (19), giving numbers for antihypertensive analyses of ≈92.7K Europeans, ≈8.1K South Asians, ≈3.5K African Caribbeans. Previous work in CPRD shows that ≈64% of people with type 2 diabetes receive statins (19), which will yield numbers for the lipid-lowering medication analyses of ≈77.1K Europeans, ≈6.7K South Asians and ≈2.9K African Caribbeans.  For people without diabetes, we expect approximately 219K people to initiate antihypertensive treatment over a similar study period to our own (20), equating to at least 94K Europeans, 6K South Asians and 3K African Caribbeans, once multipliers for ethnicity recording and the 2011 Census ethnicity breakdown are applied. From Chidwick et al (21), 113,035 people over 40 without a prior history of CVD had a high CVD risk score recorded between 2005-2013. Assuming 50% of these people had ethnicity recorded, and proportions by ethnicity are as per the 2011 census, this equates to approximately 49K Europeans, 3K South Asians and 2K African Caribbeans. |

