| L. Definition of the Study population All permanently-registered patients with research-standard data and incident type 2 diabetes Read codes from at least 1 year after 1^st^ January 2006 (start of follow-up; coinciding with when ethnicity was recorded for ≈80% of new registrations (17)) to 31^st^ December 2018 in the CPRD. The study will be restricted to incident cases to enable more precise measurement of treatment stage; people with prevalent type 2 diabetes Read codes prior to 2006 will be excluded.  Type 2 diabetes will be defined by a previously tested algorithm that uses Read codes, medication, blood test results and diabetes-specific process of care Read codes to adjudicate diabetes status (27) – see appendix. Specific exclusions will include: type 1 diabetes, gestational diabetes, non-specified diabetes diagnosed at ≤40 years in Europeans or ≤35 years in South Asians and African Caribbeans (reducing misclassified type 1 diabetes), and secondary diabetes (e.g. drug-induced).  In people without diabetes, those eligible for antihypertensive treatment will include people ≥40 years of age with incident: Read codes for hypertension, clinic BP of ≥160/100, ambulatory BP of ≥150/95 or clinic BP of ≥140/90 or ambulatory BP of ≥135/85 **plus either** 10 year CVD risk score exceeding 20% or 10% (for calendar years 2006-2013 and 2014-2019 respectively) **or** evidence of target organ disease (i.e. Read codes for left ventricular hypertrophy, chronic kidney disease, micro/ macroalbuminuria, or hypertensive retinopathy) (24). Those eligible for lipid-lowering medication will include people ≥40 years of age with an incident recording of CVD risk score ≥20% (if recorded between 2006 and 2013), or ≥10% (if recorded between 2014 and 2019), to account for guidelines changes (26)) during the study period. |

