| N. Exposures, outcomes and covariates *Data sources are listed in square parentheses*  Exposures:  For all objectives, the exposure is either South Asian or African Caribbean ethnicity (defined as above), with European ethnicity as the baseline category. *[Primary care clinical records]*  Health Outcomes by study objective:   1. Proportion of those eligible for primary prevention who are prescribed a) antihypertensives and b) lipid-lowering medication *[Primary care clinical records, prescription drug files]* 2. Time to first anti-diabetic/ antihypertensive/ lipid-lowering medication prescription. *[Primary care clinical records, prescription drug files.]* 3. Choice of a) anti-diabetic (first- to third-line), b) antihypertensive and c) lipid-lowering medications, see appendix for code lists for each (derived from chapters of the British National Formulary). *[Prescription drug files.]* 4. Doses used for each a) anti-diabetic, b) antihypertensive and c) lipid-lowering medication. *[Prescription drug files.]* 5. Monitoring rate, stratified by the time since treatment initiation, e.g. the number of a) HbA1c, b) BP or c) lipid measures divided by the amount of person time, within strata of time since initiation (i.e. first year, second year since initiation etc). *[Prescription drug files, test records.]* 6. Time to treatment intensification after detection of sub-optimal risk factor control. *[Primary care clinical records, prescription drug files, test records.]* Sub-optimal control will be classified as follows:    1. Diabetes; HbA1c≥53mmol/mol (7.5%) (7)    2. Hypertension; blood pressure≥140/80 mmHg, or 130/80 mmHg in those with neuropathy/ nephropathy or retinopathy (24)    3. Lipids; <40% reduction in non-HDL cholesterol (25) 7. Influence of the following on associations between ethnicity and prescribing: smoking, BMI, deprivation, polypharmacy, multi-morbidity, drug adherence (for outcomes iv) and v)), patient engagement with healthcare, diabetes duration and HbA1c. *[Linked IMD data, primary care clinical records, prescription drug files, test records.]*   Covariates (all taken from last entry in medical notes prior to follow-up time commencing)  Age *[Primary care clinical records]*  Sex *[Primary care clinical records]*  Smoking status *[Primary care clinical records]*  BMI *[Primary care clinical records]*  Deprivation (using patient-level IMD scores, with sensitivity analyses using practice-level IMD scores) *[Primary care clinical records, linked deprivation data]*  Polypharmacy (number of medications) *[Prescription drug files]*  Multimorbidity (defined by presence or absence of the following key co-morbidities: coronary heart disease, cerebrovascular disease, heart failure, atrial fibrilliation, hypertension, chronic kidney disease, peripheral arterial disease, retinopathy, neuropathy, cancer [any], COPD/ asthma, severe mental illness) *[Primary care clinical records]*  Patient engagement/ access (using the number of consultations in the year preceding diabetes diagnosis as a proxy) *[Primary care clinical records]*  Patient adherence (using the proportion of days covered: PDC=days of medication supplied per x day period/ x (27)). This will be calculated separately for all medications issued over the follow-up time of interest, and then a mean PDC for all medications will be derived for each patient. Both measures are important as adherence may vary by drug. *[Prescription drug files]*  Disease parameters: baseline HbA1c/ blood pressure and number of years since diabetes diagnosis *[Primary care clinical records, test records.]* |

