| O. Data/ Statistical Analysis For all parts of the study, the population will be people with and without new-onset type 2 diabetes active in CPRD from 2006 (see section K, above) and the exposure will be ethnicity (either South Asian vs. European [baseline] or African Caribbean vs. European [baseline], as detailed in section L, above). Covariates in base models will include age and sex, and further covariates will be considered individually, as outlined in section vi) below. Statistical analysis is further considered by objective:   1. **Outcome:** Proportion of those eligible for primary prevention who are prescribed a) antihypertensives and b) lipid-lowering medication   **Entry:** Date of incident a) hypertension Read code/ raised BP reading or b) elevated 10 year CVD risk score, at least 12 months after study start date of 1^st^ January 2005  **Exit:** First of; date of first antihypertensive/ lipid-lowering medication prescription (defined by the absence of a prescription for the medication in the previous 6 months’ records), end of study, leaving CPRD practice or death  **Analysis:** Proportions receiving antihypertensives/ statin will be compared by ethnicity, then logistic regression models will be used to adjust for confounding/ investigate potential mediators  **Example effect measure:** Odds ratio (OR) of receiving an antihypertensive/ lipid-lowering medication vs. not for each ethnic group of interest, stratified by time period since identification of hypertension/ elevated CVD risk   1. **Outcome**: time to initiation of first-line anti-diabetic/ antihypertensive/ statin, probability of receiving anti-diabetic/ antihypertensive/ statin at one year post-diagnosis/ identification of high CVD risk   **Entry**: date of type 2 diabetes diagnosis/ incident hypertension Read code or raised BP reading/ incident high 10 year CVD risk score recording  **Exit**: date of first anti-diabetic/ antihypertensive/ statin prescription (defined by the absence of a prescription for the medication in the previous 6 months’ records), or end of study/ leaving CPRD practice/ death  **Analysis**: summary statistics will be compared by ethnicity using Kaplan-Meier time-to-event analysis (cumulative failure probability in a given time frame by ethnicity, comparison of medians by log-rank test), Cox proportional hazards regression models will be used to adjust for confounding/ investigate potential mediators  **Example effect measure**: hazards ratio (HR) for anti-diabetic/ antihypertensive/ statin prescription   1. **Outcome:** proportions of patients prescribed medication from each anti-diabetic (stratified by first- to third-line treatment), antihypertensive and lipid-lowering class (defined by the absence of a prescription for the medication in the previous 6 months’ records)   **Sub-population:** a) all participants starting first- to third-line anti-diabetic treatment, b) all patients on antihypertensives, or c) all patients on lipid-lowering medication  **Analysis:** proportions receiving each drug will be compared by ethnicity, then logistic regression models will be used to adjust for confounding/ investigate potential mediators  **Example effect measures**: odds ratio (OR) of being prescribed metformin (=1) vs. non-metformin medication (=0) at first stage of treatment, OR of being prescribed sulphonylurea (=1) vs. non- sulphonylurea medication (=0) at second stage of treatment, OR of calcium-channel blocking antihypertensive prescription vs. non- calcium-channel blocking antihypertensive in those on antihypertensive treatment, OR of statin prescription vs. non-statin lipid-lowering medication prescription in those with >10% 10 year cardiovascular risk   1. **Outcome:** proportions of patients prescribed each dose of each anti-diabetic, antihypertensive and lipid-lowering medication, stratified by treatment stage (defined by the absence of a prescription for the medication in the previous 6 months’ records)   **Sub-population:** a) all participants on first- to third-line anti-diabetic treatment, b) all patients on antihypertensives, or c) all patients on lipid-lowering medication  **Analysis: :** proportions receiving each dose of each drug will be compared by ethnicity, then logistic regression models will be used to adjust for confounding/ investigate potential mediators  **Example effect measures**: OR of being prescribed maximum dose (2g daily) vs. sub-maximum dose of metformin, OR of being prescribed atorvastatin 10mg per day vs. higher doses (20mg, 40mg or 80mg)   1. **Outcome:** yearly monitoring rate post commencement of medication from each anti-diabetic (first- to third-line), antihypertensive and lipid-lowering class – i.e. number of times HbA1c/ blood pressure/ blood lipids measured per person-year of follow-up, stratified by year after commencement; may be multiple entry dates per person for different medications   **Entry:** first use of any medications of interest from 2006 onwards  **Exit:** first of; end of strata (e.g. 1 year after medication commencement), end of study/ leaving CPRD practice/ death  **Analysis:** summary statistics will be compared by ethnicity, Poisson regression modelling used to adjust for confounding/ investigate potential mediators  **Example effect measures**: yearly monitoring rate ratios (RRs)   1. **Outcome:** time to medication intensification (up-titration, addition or switching) after detection of sub-optimal control of diabetes, hypertension or blood lipids, or probability of intensification 1 year post-detection of sub-optimal control; may be multiple entry dates per person for different medications   **Entry:** date when sub-optimal risk factor control detected (see section M for how this is defined for each risk factor)  **Exit:** first of; date of anti-diabetic, antihypertensive or lipid-lowering treatment intensification, end of study/ leaving CPRD practice/ death  **Analysis:** summary statistics will be compared by ethnicity using Kaplan-Meier time-to-event analysis (cumulative failure probability in a given time frame by ethnicity, comparison by log-rank test), Cox proportional hazards regression models will be used to adjust for confounding/ investigate potential mediators  **Example effect measures**: cumulative failure probability for each ethnic group 1 year post detection of sub-optimal value, comparison of median survival times using the log-rank test by ethnicity, HRs of intensification stratified by year   1. **Outcome:** influence of deprivation, polypharmacy, multi-morbidity, drug adherence (iv) and v) only), patient engagement with healthcare, diabetes duration and HbA1c on any ethnic differences found in i) to v).   **Entry:** as above for i), iv) and v)  **Exit:** as above for i), iv) and v)  **Analysis:** as above for i) to v)  **Covariates:** smoking status, BMI, deprivation, polypharmacy, multi-morbidity, drug adherence, patient engagement with healthcare, diabetes duration and HbA1c  **Effect measures:** we will observe the degree of attenuation of the ethnic difference effect measure for each outcome when each covariate is inserted in turn to models, and thus evaluate the likelihood of confounding or mediation  Sub-group/ sensitivity analyses  See section O of original application  Plans for addressing misclassification and bias  See section O of original application  Multiple comparisons  See section O of original application |

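### Outcome 1 concerns primary prevention, but the amendment's eligibility, entry and exit rules for people without diabetes neither exclude established CVD nor stop at a first CVD event

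*Supplement*

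**What the plan says.** All references are to the amendment of December 2019 in the Supplement unless stated.

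- **Outcome.** Sections N and O word outcome 1 as the "Proportion of those eligible for primary prevention who are prescribed a) antihypertensives and b) lipid-lowering medication". The Objectives section describes objective 1 as incident hypertension and raised risk score, without the words primary prevention.
- **Eligibility, hypertension arm (section L).** "In people without diabetes, those eligible for antihypertensive treatment will include people ≥40 years of age with incident: Read codes for hypertension", or a clinic or ambulatory reading above a higher threshold, or a reading above a lower threshold together with a raised risk score or target organ disease.
- **Eligibility, lipid arm (section L).** "Those eligible for lipid-lowering medication will include people ≥40 years of age with an incident recording of CVD risk score ≥20"% for 2006–2013, with 10% as the threshold from 2014.
- **Exclusions (section L).** The listed ones concern type of diabetes: "Specific exclusions will include: type 1 diabetes, gestational diabetes, non-specified diabetes diagnosed at" a young age, and secondary diabetes.
- **Entry and exit for objective 1 (section O).** Entry is the incident code, reading or score. Exit is first prescription, end of study, leaving the practice or death.
- **Planning count for statins (Feasibility counts).** "113,035 people over 40 without a prior history of CVD had a high CVD risk score recorded between 2005-2013".
- **Premise on ethnicity (Technical Summary).** "ethnic minority populations without diabetes also experience an excess of most types of cardiovascular disease".
- **Models (section O).** "Covariates in base models will include age and sex". Multimorbidity, which includes coronary, cerebrovascular and peripheral arterial disease, is one of several covariates added singly to look for attenuation.

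**The concern.** A person with an earlier myocardial infarction and a new hypertension code meets section L. Treatment for that person is secondary prevention, yet the person sits in the denominator of an outcome named for primary prevention. Likewise, someone who enters free of CVD, has a stroke a year later and is then prescribed a statin counts as a primary-prevention success, because the stroke does not end follow-up.

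The stated population and the operational rule therefore disagree. This matters for an ethnic comparison because the plan itself expects more CVD in the minority groups. If the share of secondary-prevention patients differs by ethnicity, the compared proportions can differ even when primary-prevention prescribing is identical. The lipid arm also departs from its own planning population, which was free of CVD.

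**Working it through.** **1. Is the exclusion stated anywhere?** Section L lists exclusions by diabetes type only. The entry and exit rules in section O add none for CVD. The words primary prevention in sections N and O show intent but supply no code list, look-back or rule for events in follow-up. The covariates are taken from the last record before follow-up, so multimorbidity cannot capture CVD that arises between entry and prescription.

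**2. The plan's nearest stated figure.** Table 1 gives detectable effects of 1.15 and 1.18 for the proportion on statins. The European group size follows from the CVD-free count: 113,035 × 0.50 × (120.4/140) = 48,605, or about 49K. I used a two-proportion test with pooled variance, two-sided α 0.05 and power 0.90, starting from the plan's 24%:

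- South Asian, 3K vs 49K: p2 = 0.2664; OR = (0.2664/0.7336)/(0.24/0.76) = 1.150.
- African Caribbean, 2K vs 49K: p2 = 0.2721; OR = 1.184.

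Both reproduce, but as odds ratios, although the table labels them HR.

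**3. Yardstick for the hypertension proportion.** Table 1 has no row for this outcome. Using 79% treated (the complement of the plan's 21% untreated) and the plan's groups of 119.4K, 7.6K and 3.8K, the same method gives:

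- South Asian: detectable difference 0.0154; OR 1.100.
- African Caribbean: detectable difference 0.0214; OR 1.144.

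**4. Illustrative bias with no true difference in primary prevention.** Let c be the share with prior CVD. The group proportion is p = (1 − c) × p_primary + c × p_CVD. For antihypertensives p_primary is set at 0.79; p_CVD = 0.85–0.95 and every c are assumptions, because the documents give none.

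Worked example with p_CVD = 0.95 and c of 10% vs 15%:

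- European: 0.90 × 0.79 + 0.10 × 0.95 = 0.806.
- Minority: 0.85 × 0.79 + 0.15 × 0.95 = 0.814.
- OR = (0.814/0.186)/(0.806/0.194) = 1.053.

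| Prior CVD, European vs minority | OR at p_CVD 0.85 | OR at p_CVD 0.95 |
|---|---|---|
| 10% vs 10% | 1.000 | 1.000 |
| 1% vs 2% | 1.004 | 1.010 |
| 10% vs 15% | 1.019 | 1.053 |
| 10% vs 20% | 1.038 | 1.112 |
| 10% vs 5% | 0.982 | 0.951 |

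Only the widest gap with the highest p_CVD exceeds the detectable OR of 1.10, and none reaches 1.14.

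**5. Lipid arm.** With p_primary = 0.24 and p_CVD assumed at 0.50–0.80, shares of 1% vs 2% give ORs of 1.01–1.03, and 10% vs 15% give 1.07–1.14. The larger shares have no support in the documents, since entry needs a recorded 10-year risk score and the only comparable population described is CVD-free.

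**6. Precision after the exclusion.** Removing an assumed 5%, 10% or 20% from all hypertension groups moves the detectable OR from 1.100 to 1.103, 1.106 or 1.113 (South Asian), and from 1.144 to 1.148, 1.152 or 1.162 (African Caribbean). The statin figures do not change.

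**The case against.** The strongest reply is that the restriction is already there: outcome 1 is limited in words to primary prevention, the statin planning population is CVD-free, and CVD code lists are in the appendix. A careful analyst would probably apply the filter. That stands as evidence of intent. It does not settle the rule, because section L is where eligibility is made operational, and two analysts could build different cohorts from it.

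The reply is also right that multimorbidity adjustment gives some sight of the problem. But that adjustment leaves the denominator as it is, is not in the base model, and would present a population error as confounding or mediation.

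Three stronger readings are tempting and are not supported:

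- **That the results will be biased by a known amount or in a known direction.** The documents give no prior-CVD prevalence by ethnicity among eligible people. The premise covers most types of CVD, not all, so the sign for a given group is open. The 79% is also not stated to be a CVD-free figure, and the illustration is not adjusted for age and sex.
- **That a spurious OR of 1.05 exceeds the plan's detectable HR of 1.02.** That row concerns time to antihypertensive initiation, a different outcome on a different scale. It also reproduces only with equal allocation (1.021); the actual allocation gives 1.044 and 1.062.
- **That CVD patients already on treatment would pull the ORs to 0.93 (statins) or 0.83 (antihypertensives).** These come from 0.216 vs 0.204 and 0.711 vs 0.6715, which count every CVD patient as a non-starter. That is mainly a question of how existing users are handled, and excluding CVD would not resolve it for users without CVD.

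**Conclusion.** The concern holds as a conflict between the stated population of outcome 1 and the eligibility, entry and exit rules for people without diabetes. It is clearest in the hypertension arm. The lipid arm is less exposed.

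Unequal composition by ethnicity is plausible on the plan's own premise, but its effect is not quantified by the documents. Under the assumptions shown, the spurious antihypertensive OR is about 1.02–1.11 for 10% vs 15–20% prior CVD. It is negligible when the shares are close, and below 1 if the minority share is lower. That is mostly under the detectable ORs of about 1.10 and 1.14, though it can reach the same order.

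This is a cheap correction worth making before the cohort is built. It does not invalidate the design.

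**What to change.** - **Section L, objective 1, people without diabetes:** exclude anyone with a code for coronary heart disease, cerebrovascular disease or peripheral arterial disease on or before the entry date, using the code lists already in the appendix.
- **Section O, objective 1:** add the first such code to the exit events, so that later prescriptions are not counted as primary prevention. Say how people who leave by this route before a prescription enter the logistic model; the same statement can cover death and leaving the practice.
- **Objective 2:** apply the same rules to the antihypertensive and statin time-to-initiation analyses in people without diabetes only where these are reported as primary prevention. The plan does not describe objective 2 that way. Leave the anti-diabetic analysis unchanged, since a blanket exclusion could remove people with both diabetes and CVD from it.
- **Objectives section:** align the wording of objective 1 with sections N and O.
- **Optional:** report people with prior CVD as a separate stratum.

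The cost is a few sentences, a filter on existing code lists and a slightly smaller hypertension denominator. The loss of precision is small and the statin planning numbers stand.
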